**Table 5. Statistical Power for Exploratory Subgroup Analyses**

| Subgroup sample size in each treatment group | Power to detect 5-point difference between in store and combination online/in-store POP arms* |
|----------------------------------------------|-----------------------------------------------------------------------------------------------|
| 52, 52                                       | 80%                                                                                           |
| 60, 40                                       | 77%                                                                                           |
| 40, 40                                       | 69%                                                                                           |
| 50, 30                                       | 66%                                                                                           |
| 30, 30                                       | 56%                                                                                           |

\*Note that secondary analyses should be considered exploratory as the alpha error will not be contained at 0.05.

#### **g. Data Storage and Confidentiality**

Upon oral consent, each participant will receive a unique, study ID number. The study ID number will be generated in the following format: three-letter identifier (e.g. LEB for Lebanon) followed by the participant number (0001, 0002, 0003, etc.). All subsequent participant research materials (including surveys and data collection tools) will only include participant ID numbers. Identifiable participant information will be stored in a screening log maintained by the study team. Participant identification will be limited to the SuperWIN research coordinators, SuperWIN project manager, CCHMC Bionutrition Core staff, Grocery Runners staff, study store TLC staff, and 84.51 (Kroger's analytics company, 84.51°).

Except for 84.51°, these individuals will have direct contact with participants. At study visits, TLC RDNs will be able to also review each participant's collected data, including the baseline Demographic, Pre-Intervention, and Medical History Survey findings, baseline diet intake data, baseline biometric data, and updated purchase data.

The CCHMC Data Management and Analysis Center (DMAC) staff will ensure the safe transfer and storage of participant data (including to and from 84.51°). Urgent (e.g. participant reports of syncope due to hypoglycemia) and nonurgent (e.g. baseline LDL-C 240 mg/dL) safety issues will result in notification of the participant's primary care provider (section 6b - *Safety Considerations*).

During the course of the study, information collected over the phone or electronically will be made available to key research personnel through a secure, file transfer protocol site. This includes scheduled visit dates and times, survey data, biometric data, dietary intake data, and purchase data. Diet intake and participant purchase history data will be stored on a secure server. It will then be merged together using SAS with data from REDCap for reporting and analyses.

Upon conclusion of the study, this information will be de-identified except for participant ID and Kroger Loyalty ID numbers. Any and all paper copies containing participant information (created in the event of computer or technical issues) will be promptly entered and stored in a locked file cabinet by the research coordinator or project manager. All electronic data will be stored on a secure server to be kept indefinitely by the investigators. Data and patient identifiers (e.g. name, home street address, birthdate, telephone numbers, email address, electronic health record number, dates of study procedures) will be deleted from staff computers and the recycle bin emptied. Hard-copies of completed surveys and other data collection tools will be kept in a locked file cabinet for 5 years after the conclusion of the study, after which they will be shredded.

#### **h. Setting and Facilities**

Each participant will be assigned to the Kroger study store at which the participant conducts his/her regular grocery shopping. Each study visit will be conducted at TLC in each store, across the Cincinnati and Northern Kentucky regions.

TLC is an independent medical clinic located within Kroger supermarkets, staffed by board-certified nurse practitioners, physician assistants, and registered dietitian nutritionists qualified to diagnose and treat minor medical issues. All medical assessments, including height, weight, waist and hip circumferences, blood pressure, blood lipid panel, and blood glucose

measurements will be made by a RDN or nurse in a private patient consultation room within TLC.

Dietary intake recall data will be collected via phone call from trained interviewers at the Bionutrition Core of the Schubert Research Clinic at CCHMC.

**i. Estimated Period of Time**

The entire research project will take an estimated 2.5 years to complete after UC IRB approval.

**6.RISK/BENEFIT ASSESSMENT**

**a. Level of Risk**

**Table 6. Intervention Risks**

| Risk or Discomfort                                                                                                                                                                                                                                                                                                          | Level   |
|-----------------------------------------------------------------------------------------------------------------------------------------------------------------------------------------------------------------------------------------------------------------------------------------------------------------------------|---------|
| Physical – finger stick blood lipid panel and glucose measurement

Use of a finger stick is less invasive and takes less time than laboratory tests done at a physician's office. A finger stick requires significantly less blood and uses a smaller needle, than a typical blood draw done at a physician's office. | Minimal |
| Physical – blood pressure measurement

The blood pressure cuff may cause some discomfort while constricting to measure blood pressure. This discomfort is no greater than that experienced at a physician's office when measuring blood pressure.                                                                     | Minimal |
| Emotional – nutrition counseling

Participant may feel some embarrassment or frustration when discussion their eating habits, food budget, or food purchasing habits with a registered dietitian.                                                                                                                     | Minimal |

## **b. Safety Considerations**

All participants will undergo biometric assessments (height, weight, waist and hip circumferences, blood pressure, blood lipid panel, and blood glucose) at Day 0. All assessments, except height, will be repeated at Day 84 and Day 180. If a study participant exhibits abnormal biometric values or complains about a new and/or an exacerbation of pre-existing symptoms, their PCN provider will be contacted by the study team. Any contacts/referrals made for safety considerations will be captured in a contact log. The following are examples that would warrant immediate PCN provider contact: SBP  $\geq 220$  mm Hg, SBP  $\leq 80$  mm Hg, DBP  $\geq 130$  mm Hg, blood glucose  $\leq 60$  mg/dl or  $\leq 80$  mg/dl with hypoglycemic symptoms, new-onset chest pain, severe fatigue or weakness, new-onset lightheadedness/dizziness or syncope, new-onset or persistent nausea, acute visual changes, worsening depression, or new-onset hypertension. In case of an emergency (as determined by the assessor), 911 would be called.

PCN providers will be given the names of their patients who have been randomized into the trial.

## **c. Direct Benefit to Participants**

All participants will benefit from nutrition education, both from the individualized nutrition counseling as well as the provided education materials. Participants will also benefit from receiving 3 biometric assessments at TLC. Participants will be informed of their biometric assessment results (see Biometric Assessment Form) and may share this information with their providers, if they choose to do so. All of the above benefits will be provided at no cost to the participant.

The risk or discomfort in this study is no greater than that a participant would encounter at a medical office visit or nutrition counseling session.

## **7. PAYMENT**

Participants will receive 2 incentives in separate installments. After the completion of the second set of 3 dietary recalls following Day 84, he/she will be mailed a \$25 pre-paid debit Greenphire clincard. After the completion of the third set of 3 dietary recalls by Day 180, each participant will receive another \$25 uploaded to his/her clincard. Participants who do not complete all 3 recalls at each time-point will not receive any monetary incentives. Clincards in the amounts of \$25 and \$25 are an appropriate, convenient, and non-coercive form of payment.

## **8.SUBJECT COSTS**

As part of the nutrition education, participants will be encouraged to change food purchasing and eating habits to better align with a dietary pattern conducive to healthy living and decreased cardiovascular risk. Participants will be responsible for the cost of purchasing their own groceries. Participants will also be responsible for any costs associated with transportation to and from their selected Kroger study site.

Participants randomized to the combined online/in-store POP education arm will be encouraged to shop through Kroger's online shopping platform using their personal electronic devices and Internet connection. They will be provided with home grocery delivery services through The Grocery Runners, an independent home delivery company that provides services in Dayton, Cincinnati, and Northern Kentucky. The costs of shopping online will be minimized. The use of The Grocery Runners services will be provided at no cost to the participant.

## **9.CONSENT FORM**

### **a. Consent Process**

The consent process is broken down into four parts: 1) review of the recruitment packet; 2) verbal consent; 3) written consent; and 4) focus group consent.

A recruitment packet will be sent to potentially eligible UC Health PCN patients (see HIPAA Waiver for Recruitment). The packet will contain 1) the Letter from Study Team (see attached) and 2) the ICF (see attached). The ICF will be provided so participants can review it and discuss their questions at Visit #1 with the RDNs. Patients who receive the recruitment packet will be encouraged to call the study team if they are interested. The contact information for the study team is listed on the letter.

All interested participants who call the study team will first undergo a verbal consent process (see Telephone Screening Script). All individuals who are recruited through Methods 2-5 (postcard, PCP flyer, phone call, or through Kroger marketing) will also undergo a verbal consent process. During this process, the study manager or study coordinator will review the Telephone Screening Script with the participant. The study team member will prompt the patient to ask any

questions he/she may have in between each section of the script. Upon review of the verbal consent process, the research team member will ask for verbal consent to participate in the study. The research team member will document whether oral consent was obtained in REDCap. The script will obtain verbal consent for study procedures completed before Visit #1. If the participant provides verbal consent, the participant will be assigned a participant ID number. If the participant does not provide verbal consent, they will be considered a prescreen-failure and this data will be captured in the form of a screening log. Once the participant provides verbal consent, he/she will be screened for eligibility. The study team will continue to review general eligibility with the participant and, if he/she remains eligible, Visit #1 will be scheduled at the conclusion of the phone call.

At Visit #1, the participant will be given time to review the ICF with the RDN. The RDN will review the key points of the ICF, including the study purpose, participant involvement, risks, benefits, confidentiality, cost, payment, and rights. The RDN will prompt the patient to ask any questions he/she may have in between each section of the ICF. If the participant declines to participate at Visit #1, or if eligibility criteria are not met, he/she will be considered a screen-failure, with this captured in REDCap. If the participant gives written consent to participate in the rest of the study, the RDN will conduct the remainder of the Visit #1 procedures. The participant will be given a copy of the ICF. The original ICF will be stored at TLC in a secured location.

The participant will be informed that choosing to participate or not participate will not affect his/her relationship (including purchases) with Kroger or their affiliates, nor any medical care he/she may receive from TLC or UC Health. Each participant will be given the option for re-contact at Day 180.

For the focus groups, participants who complete SuperWIN as part of an intervention group will review the focus group informed consent with the dietitian at the Day 180 visit. If the participant agrees to attend the focus group, the dietitian will give them the purchasing snapshot questionnaire to be completed at home. All completed focus group informed consents will be collected by the study team and will be kept in a study binder. Further details surrounding the focus groups can be found in the focus group protocol.

#### **b. Consent Form**

See attached Telephone Screening Script, Informed Consent Form, Focus Group Informed Consent Form, and Day 180-Re-contact Sheet.

## **11.ADDITIONAL DOCUMENTATION**

- 1) NIH Biosketch [name]
- 2) NIH Biosketch [name]
- 3) HIPAA Partial Waiver for Recruitment
- 4) Letter from Study Team V1.0
- 5) Informed Consent V1.0
- 6) Postcard V1.0
- 7) Recruitment Ad Flyer V2.0
- 8) Recruitment Ad Tear Pad V2.0
- 9) Telephone Screening Script V1.0
- 10) Demographic Survey V1.0
- 11) Medical History Survey V1.0
- 12) Pre- and Post-Intervention Survey V1.0
- 13) Food Amounts Booklet V1.0
- 14) Links to Handouts and Videos
- 15) POP Checklist V1.0
- 16) DASH Goal Tear Sheet V1.0
- 17) Goal Tracking Form V1.0
- 18) Biometric Assessment Form V1.0
- 19) Process Evaluation Survey V1.0
- 20) Request for Waiver of Consent Documentation
- 21) Request for Waiver of Consent Process
- 22) Focus Group Protocol
- 23) Focus Group Informed Consent Form
- 24) Focus Group Information Sheet
- 25) Focus Group Questions
- 26) Purchasing Snapshot Questionnaire
- 27) Day 180 Re-contact Sheet

### Raw Data Check

It will involve all variables and all time-points. The raw data check will consist of the following:

|                       |                                |
|-----------------------|--------------------------------|
| Continuous Variables  | N, N-Missing, Min, Median, Max |
| Categorical Variables | N, N-Missing, Count, Percent   |

The purpose of the raw data check is to examine data for outliers, missingness, and distributional properties. These will be described and (if necessary) adjusted for in the analyses. Histograms and bar charts may be produced.

### Overall Analysis Approach

Descriptive Statistics. Descriptive statistics will consist of mean and standard deviation (SD) and median and interquartile range (IQR) for variables. Counts and percentages will be used for categorical variables. Unless otherwise determined, descriptive statistics will be produced for all variables and all time-points.

Distributions/Transformations. Residuals from models will be examined for primary and key secondary outcomes for distributional properties, to ensure model assumptions (normality and independence of residuals) are met. If they are not met, data transformation or other analysis methods (e.g. nonparametric) will be used.

Treatment Groups. Subjects were randomly assigned to one of three treatment groups: 1) Control; 2) In-store Point-of-Purchase Education (POP1); and 3) Combined Online and In-store Point-of-Purchase Education (POP2). The designation POP1/POP2 will be used to denote the combining of data from POP1 with POP 2.

Primary Outcome and Comparison: The primary outcome is the DASH score. The primary comparison of interest is the change in DASH score between baseline and the 3-month follow-up.

Key Secondary Outcomes: The main secondary outcomes are BMI, SBP, DBP, non-HDL cholesterol, total cholesterol and triglycerides.

Modeling. The primary comparisons will use a mixed model for repeated measures. This multivariable model, controlling for covariates, will have DASH score as the dependent variable with treatment as the independent variable. The primary treatment group comparisons will be performed using appropriate contrasts of the treatment arm estimates.

Significance Level ( $\alpha$ ) and Tests. For the primary and key secondary endpoints, hierarchical testing will be used, first comparing Control vs. POP1/POP2. If  $p < 0.05$  for that test, then the two intervention groups will be compared (POP1 vs. POP2). This will preserve an alpha-error of 0.05. For all other endpoints, testing will be done at the  $\alpha = 0.05$  significance level, with no multiple comparison adjustments. All tests, unless otherwise noted, will be two-sided.

COVID-19 Impact Analysis. Due to the COVID-19 pandemic occurring during the course of the SuperWIN, we have a COVID-19 impact analysis following regulatory guidance, defined below.

Software. Unless otherwise specified, SAS® 9.4 TS1M5 (SAS, Inc., Cary, NC) software will be used for all analyses.

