| Change (baseline to 6 mon)                                                                                                                                                                                                                                                                                                                                                                                                                                                                                                         | -395.4 (-699.6, -91.3)                    | -377.8 (-587.7, -167.8)                       | -461.4 (-666.1, -256.7)                       | -24.1 (-360.8, 312.5)                                                                     | 0.89           | -83.7 (-380.7, 213.3)                                                     | 0.58           |
| Strategy 1: In-store education only. Strategy 2: In-store education plus online training and tools. A mixed model for repeated measures was used to model each outcome, controlling for age-group, sex, household size, race, income and baseline BMI. Contrasts (with two-sided t-tests) were used to estimate differences between treatment groups for 6-month change from baseline. Intervention effect is difference in mean change in outcome and 95% confidence interval. No adjustments for multiple comparisons were made. |                                           |                                               |                                               |                                                                                           |                |                                                                           |                |

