#### **f. Statistical Analysis**

A minimum of 250 adults will be randomized into the study. Approximately 100, 100, and 50 participants will be randomized to the in-store POP education arm, the combination online/in-store POP education arm, and the control arm, respectively (see section *Data Analysis and Data Monitoring* for power calculations and testing plan).

NDSR food data will be used to calculate overall diet quality using the DASH score. The DASH score is a modification of the DASH index developed by Gunther et al. [11]. DASH score is a continuous 90-point measure with higher scores equating to higher DASH diet adherence.

Randomization will use stratification to balance important baseline covariates among study groups. These covariates will be age, sex, and household size.

Data will initially be assessed for their distribution (e.g. normality) and the level of missing values. Descriptive statistics will be calculated for each arm. The primary endpoint will be the change from baseline to Day 90 in the DASH score (as assessed by dietary intake recalls). Using hierarchical testing, up to 2 tests will be performed:

- 1) First test: Any POP education arm vs. control arm
- 2) Second test: In-store POP education arm vs. combined online/in-store POP education arm

An intention-to-treat (ITT) analysis will be used for both tests. The “last observation carried forward” approach will be used for missing data. Ascertainment of DASH score at Day 90 for each participant will require completion of at least 1 of 3 dietary intake recalls. Sensitivity analyses may be performed using a “complete case” approach or multiple imputation techniques.

The primary comparisons will use an analysis of covariance (ANCOVA) model. This multivariable model, controlling for the baseline covariates, will have DASH score as the dependent variable with treatment arm as the independent variable. As part of this process, the normality of distribution of DASH scores at both baseline and Day 90 will be assessed. If necessary, transformations (e.g. log) will be used to satisfy the assumptions of the model. The primary treatment group comparisons will be performed using appropriate contrasts of the randomization arm estimates. Statistical testing will only be performed for the second test if  $p < 0.05$  is met for the first test (i.e. hierarchical testing). This will preserve an alpha-error of 0.05.

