## Diet: Baseline, 3 month and 6 month

Statistics for continuous variables are shown as least squares means (CI). Values for categorical variables shown as N (%).

|                                    | Control
(n=46) | POP1
(n=100) | POP2
(n=101) | Intervention Effect (CI)
POP1/POP2 vs. Control | P-value | Intervention Effect (CI)
POP1 vs. POP2 | P-value |
|------------------------------------|-------------------|-----------------|-----------------|---------------------------------------------------|---------|-------------------------------------------|---------|
| DASH Score                         |                   |                 |                 |                                                   |         |                                           |         |
| At baseline                        |                   |                 |                 |                                                   |         |                                           |         |
| At 3 mon                           |                   |                 |                 |                                                   |         |                                           |         |
| At 6 mon                           |                   |                 |                 |                                                   |         |                                           |         |
| Change (baseline to 3 mon)         |                   |                 |                 |                                                   |         |                                           |         |
| Change (baseline to 6 mon)         |                   |                 |                 |                                                   |         |                                           |         |
| Fruit servings/1000 kcal/day       |                   |                 |                 |                                                   |         |                                           |         |
| At baseline                        |                   |                 |                 |                                                   |         |                                           |         |
| At 3 mon                           |                   |                 |                 |                                                   |         |                                           |         |

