| Hypertension control at 6 mon – N (%)b |                   |                 |                 |                                                   |         |                                           |         |
| SBP <120 and DBP <80                                     |                   |                 |                 |                                                   |         |                                           |         |
| SBP <130 and DBP <80                                     |                   |                 |                 |                                                   |         |                                           |         |
| SBP <140 and DBP <90                                     |                   |                 |                 |                                                   |         |                                           |         |
| SBP <150 and DBP <90                                     |                   |                 |                 |                                                   |         |                                           |         |

POP1: In-Store Only Arm. POP2: In-Store and Online Arm.

For systolic blood pressure and diastolic blood pressure: a mixed model for repeated measures was used to model each outcome, controlling for age-group, sex, race, baseline BMI, baseline BP meds (0, 1, 2+), baseline sedentary (yes/no), and baseline current smoking (yes/no). Contrasts were used to estimate differences between treatment groups a) at baseline, b) for 3-month change from baseline, and c) for 6-month change from baseline.

For hypertension control, relative risk was calculated using logistic regression models, controlling for the baseline value of the dependent variable (e.g. SBP, DBP), age-group, sex, race, baseline BMI, baseline BP meds (0, 1, 2+), baseline sedentary (yes/no), and baseline current smoking (yes/no).

a Intervention effect is difference in mean change in blood pressure and 95% confidence interval.

b Intervention effect is the relative risk and 95% confidence interval.

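### The primary mixed model appears to leave baseline DASH as a free outcome in each arm, so the 3-month contrast is in effect a change score that gives up precision and over-corrects chance baseline differences

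*Combined protocol and SAP*

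**What the plan says.** The SAP (Overall Analysis Approach) makes the DASH score the primary outcome and adds: "The primary comparison of interest is the change in DASH score between baseline and the 3-month follow-up". The model is a mixed model for repeated measures, described as follows: "This multivariable model, controlling for covariates, will have DASH score as the dependent variable with treatment as the independent variable". Neither the covariates for DASH nor the handling of baseline DASH is stated.

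The structure has to be read from other places:

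- **DASH table shell** (SAP, Diet). It has rows for baseline, 3 months, 6 months and both changes in each arm, and says: "Statistics for continuous variables are shown as least squares means (CI". Baseline is therefore a modelled value.
- **Blood pressure footnote** (SAP). "Contrasts were used to estimate differences between treatment groups a) at baseline, b) for 3-month change from baseline". The SAP footnote for weight, BMI and waist-to-hip ratio has the same structure. Neither mixed-model covariate list contains the baseline value of the outcome. The logistic models in the blood pressure footnote do have it: "controlling for the baseline value of the dependent variable (e.g. SBP, DBP".
- **Table S10**, for the DASH components as reported: "A mixed model for repeated measures was used to model each outcome, controlling for age-group, sex, household size, race, income and baseline BMI". Baseline component values are not in the list.

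Protocol section 5f plans an ANCOVA that controls for the baseline covariates. It names them where it describes the stratified randomisation: "These covariates will be age, sex, and household size". Baseline DASH is not listed there.

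**The concern.** If baseline is a response with a free mean per arm, the treatment effect on change is the difference between two within-arm changes. Such a contrast subtracts the whole baseline difference between arms. A baseline-adjusted analysis subtracts only the part that carries over to follow-up, which is smaller whenever the correlation between the two measurements is below 1.

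Two things are at stake. The first is precision, in a design whose control arm has about 50 participants. The second is that each realised estimate depends on where that small control arm happened to start: if it starts high, the change score favours the interventions, and if it starts low, it works against them. A further question is whether the phrase about controlling for covariates has any effect on the estimate.

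**Working it through.** **1. The plan's own power.** Inputs from protocol 5f: difference 5, SD 9 for the change endpoint, two-sided alpha 0.05. For 200 v 50, SE = 9 × √(1/50 + 1/200) = 1.423 and 5/1.423 = 3.51. The noncentral t gives 93.8%, against the stated 93%. For 100 v 100 it gives 97.4%, against 97%. Both figures reproduce.

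**2. Is baseline free?** Table S18 prints baseline DASH least squares means of 45.1 (control), 42.6 (Strategy 1) and 42.7 (Strategy 2). A model with baseline only as a covariate would have no such means, and a constrained model would make them equal. The contrast follows from the printed means: [(53.2 − 42.6) + (56.4 − 42.7)]/2 − (48.9 − 45.1) = 12.15 − 3.8 = 8.35, printed as 8.3. This sum confirms that the reported effect is a difference in change. It says nothing about how other covariates enter, because it holds in any linear model.

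**3. What covariates do in that model.** Write the mean for a participant in an arm at a visit as μ(arm, visit) + γx. The contrast is [μ(POP, 3) − μ(POP, 0)] − [μ(control, 3) − μ(control, 0)], and γx cancels. In simulation with 46/100/101 participants, three visits and complete data, the model contrast equalled the raw difference in mean change to rounding error. With missing follow-up the equality is approximate. Table S9 gives 3-month diet data for 42 + 92 + 91 = 225 of 247, so 22 are missing. If covariates enter by visit, they do not cancel.

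**4. Information lost.** Assume equal SDs s and correlation ρ between baseline and 3 months.

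- Change score variance: 2s²(1 − ρ)
- Baseline-adjusted variance: s²(1 − ρ²)
- Ratio, adjusted to change score: (1 + ρ)/2, so the information lost is (1 − ρ)/2

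ρ is not in the documents. Rough pointers:

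- The change SD in step 5, with a 3-month SD of about 10.3 from the Table S20 intervals, gives ρ = 1 − 10.45²/(2 × 10.3²) ≈ 0.49.
- A common SD of 12 would give 0.62.
- The baseline-DASH split in Table S20 suggests a slope of about 0.25 to 0.34.

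I use 0.3 to 0.7.

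**5. Change SD implied by Table S18.** With t = 1.984:

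- Strategies v control: SE = (13.3 − 3.4)/2/1.984 = 2.495. Dividing by √(1/22 + ¼(1/45 + 1/42)) = 0.2387 gives 10.45.
- Strategy 2 v 1: SE = (7.6 + 1.3)/2/1.984 = 2.243. Dividing by √(1/45 + 1/42) = 0.2146 gives 10.45.

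**6. Power for 5 points, 200 v 50, at that SD** (adjusted SD = 10.45 × √((1 + ρ)/2)):

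| Analysis | Information lost | SD | Power |
|---|---|---|---|
| Change score | – | 10.45 | 85% |
| Adjusted, ρ = 0.3 | 35% | 8.43 | 96% |
| Adjusted, ρ = 0.5 | 25% | 9.05 | 94% |
| Adjusted, ρ = 0.7 | 15% | 9.63 | 90% |

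The loss is what the change score gives up relative to the adjusted analysis. At the planned SD of 9, adjustment would raise 93.8% to between 99.1% (ρ = 0.3) and 96.7% (ρ = 0.7).

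**7. Illustration, pre-COVID subgroup only.** The baseline difference is 42.65 − 45.1 = −2.45 and the 3-month difference is 54.8 − 48.9 = 5.9. The adjusted effect is 5.9 + slope × 2.45: 6.6 at slope 0.3, 7.1 at 0.5 and 7.6 at 0.7, against 8.35 at slope 1, which is the change score.

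**The case against.** The strongest reply is that the SAP sentence does not exclude baseline DASH and that the full-trial 3-month DASH table is not in the documents, so the structure is inferred. That is fair as far as the sentence goes. But the shell, the footnotes and the unequal baseline means all point the same way, and nothing in the SAP points the other way.

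It can also be said that change from baseline is the declared endpoint, that a change-score test is unbiased over randomisation, and that type I error is unaffected. All of this stands, and it makes the point one of efficiency rather than validity.

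A reader might infer more than the documents support:

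- **That the trial is underpowered against its plan.** It is not: the 93% rests on a change SD of 9 and reproduces. The 85% uses an SD seen afterwards in 109 participants.
- **That a quarter of the information is lost.** That is the ρ = 0.5 case only.
- **That adjustment restores exactly 93%.** The adjusted power also depends on the unknown ρ.
- **That chance imbalance is left in uncorrected.** It is over-corrected.
- **That the primary estimate is biased.** The shift in step 7 comes from an exploratory subgroup, and the whole-trial DASH baseline difference is not given.
- **That the stratification factors certainly do nothing.** They cancel only if entered as main effects, and the SAP does not say how they enter.
- **That the protocol's ANCOVA excludes baseline DASH.** It is silent, and it does plan to check the baseline DASH distribution.

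The missing household size is a small matter. The SAP blood pressure footnote reads "controlling for age-group, sex, race, baseline BMI, baseline BP meds (0, 1, 2+), baseline sedentary (yes/no" and does not include it, but the models reported in Tables S14 and S15 do. As a main effect it would cancel from the change contrast in any case.

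**Conclusion.** The point holds as a matter of efficiency and specification. Read together, the documents indicate a free-baseline mixed model whose 3-month contrast is in effect a change-score comparison, exactly so with complete data and main-effect covariates, and approximately so with 22 of 247 missing. The test is valid and the power statement is consistent with its own assumption.

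Relative to a baseline-adjusted analysis, 15% to 35% of the information is given up. This assumes equal SDs at the two times and a correlation of 0.3 to 0.7. At the change SD of about 10.45 from the pre-COVID subgroup, adjustment would move power for 5 points from about 85% to between 90% and 96%. Every correlation in that range favours adjustment. In that subgroup alone, the printed effect of 8.3 would be about 6.6 to 7.6. The change should be made, but the plan is not invalid without it.

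**What to change.** Specify the primary model as a mixed model for repeated measures on the 3- and 6-month DASH scores, with arm by visit, baseline DASH by visit, and age group, sex and household size by visit. Alternatively, keep baseline as an outcome but constrain its mean to be equal across arms, with the three stratification factors still entered by visit.

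- Keep the same two hierarchical contrasts.
- List the DASH covariates in the SAP.
- Use the same structure for the key secondary outcomes, and add household size to the SAP blood pressure models so that they match the stratification and the reported tables.
- Keep the change-score contrast as a sensitivity analysis.

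The cost is SAP wording and a few lines of code. Every variable is already collected, and the sample size and testing order do not change.
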